#### Primary outcomes

2.6.1

(1)Changes in SBP and DBP (mm Hg) measured with an electronic sphygmomanometer. The average value of 3 measurements will be used.(2)Percentage changes in the dose of antihypertensive drugs. At each regular visit, the community doctors will determine whether the dose of antihypertensive drugs needs to be adjusted according to changes in blood pressure during the last month and will record the adjustment.

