### Study visits

2.8

During the 1-year follow-up period, the investigators will visit the patients monthly at the community health service centers, which are generally within 1 km of the patients’ homes. At month 0 (baseline visit), we will collect demographic characteristics (name, phone number, sex, age, education level, height, and weight) and disease-related characteristics (SBP, DBP, course of hypertension, comorbidities, smoking, drinking, and type and dosage of antihypertensive drugs currently used). At months 6 and 12, we will measure blood pressure, changes in doses of antihypertensive drugs, quality of life, blood and urine indicators, and AEs. The other regular visits (ie, months 1–5 and 7–11) will involve the distribution of moxa rolls and moxibustion boxes to patients, the assessment of patient compliance and the adjustment of the doses of antihypertensive drugs. A detailed schedule of the study visits is shown in Figure 2.

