### Sample size calculation

2.11

We used the expected reduction in SBP as a reference and a sample size formula for continuous outcomes in nonrandomized controlled studies to estimate the minimum required sample size. Based on the results of our pilot observations and experts’ advice, we expect to measure a 5 mm Hg change in SBP with a standard deviation of 20 mm Hg. Setting the probabilities of type I error and type I error of 0.05 and 0.20, respectively, and considering a 20% attrition rate, the minimum sample size is calculated to be 140 per group. As we have sufficient funding, we increase the expected sample size to 300 cases per group to allow adjustment for more confounders.

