### Statistical analysis plan

2.12

The analyses of the primary outcomes will be performed in the intention-to-treat population where either patients in the control group who performed heat-sensitive moxibustion or patients in the heat-sensitive moxibustion group who stopped moxibustion during follow-up will still be kept in their original group. Meanwhile, we will also perform sensitivity analyses using the perprotocol population to test the robustness of the main analysis. All analyses of the secondary outcomes will be performed in the per-protocol population. We will decide whether to impute missing data and which method should be used to impute missing data based on the actual distribution of the missing data.

For categorical or ordinal variables, we will calculate frequencies and percentages as the descriptive statistics and compare the between-group differences using the chi-square test or the linear-by-linear association test. We will present the means with standard deviations/errors and medians with interquartile ranges for continuous variables with normal and skewed distributions, respectively; the independent *t* test or the Mann-Whitney *U* test will be used to compare 2 groups. The effects of heat-sensitive moxibustion on the outcomes will be inferred using analysis of covariance or a logistic regression model adjusted for age, course of hypertension, baseline SBP, comorbidities, education level, smoking status, drinking status, and types of antihypertensive drugs recoded as dummies. The effects will be measured as the mean difference or odds ratio with a 95% confidence interval, and *P*-values will also be calculated. In addition, we will test 2 subgroup hypotheses:

(1)the dose of moxibustion: ≥3 sessions/wk vs <3 sessions/wk;(2)whether the heat-sensitive sensation appears: yes vs no.

The significance level indicating a difference between groups and subgroups will be α = 0.05. We will use R version 4.0.2 (The R Foundation for Statistical Computing, Austria) to run all statistical analyses.

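### Three primary variables share one blanket alpha of 0.05, with no primary visit and no rule for which result decides the study

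*Protocol article*

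**What the plan says.** Section 2.6.1 of the Protocol article puts two items under the primary outcomes. The first holds two variables: "Changes in SBP and DBP (mm Hg) measured with an electronic sphygmomanometer". The second is "Percentage changes in the dose of antihypertensive drugs". That makes three primary variables.

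Section 2.8 schedules them twice after baseline: "At months 6 and 12, we will measure blood pressure, changes in doses of antihypertensive drugs, quality of life". Neither visit is called primary.

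Section 2.12, which is headed as the statistical analysis plan, sets the level: "The significance level indicating a difference between groups and subgroups will be α = 0.05". On estimation it says "The effects will be measured as the mean difference or odds ratio with a 95% confidence interval". It gives no order, no division of alpha and no statement of how many of the primary results must be significant.

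Section 2.11 plans the size on one of the three: "We used the expected reduction in SBP as a reference". SBP is not declared there or elsewhere to be the sole, first or deciding primary outcome.

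**The concern.** A significance level controls the error of the conclusion it is attached to. Here the planning alpha belongs to one SBP comparison, but the article lets the primary conclusion rest on SBP, DBP or dose, at a visit it does not name. As written, a significant result on any of the three could be reported as the positive primary result, and nothing in the text would contradict that report.

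The choice has consequences. The Discussion says that significant efficacy might allow moxibustion to replace part of the drug treatment, and that the findings may affect government decisions on public health. A reader of the results needs to know in advance which finding would support such a statement.

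The way dose is handled makes the gap more than formal. Under section 2.6.1, community doctors adjust drug dose in response to blood pressure. A benefit could therefore appear as lower pressure, as lower dose, or partly as each. With no rule fixed beforehand, the reading can follow whichever appears.

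**Working it through.** **Inputs.** From section 2.12: alpha 0.05 per comparison, taken as two-sided because the intervals are 95% (sidedness is not stated). From section 2.6.1: three primary variables. From section 2.8: two follow-up visits. From section 2.11: SBP difference 5 mm Hg, SD 20 mm Hg, alpha 0.05, type II error 0.20 (printed as a second type I error), 20% attrition, 140 per group minimum, 300 per group planned. The article gives no correlations. Assumed ranges: SBP with DBP 0 to 0.8; blood pressure with dose 0 to 0.3; between visits 0 to 0.9.

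**The plan's own figure.** For two means, n = 2 × (1.960 + 0.842)² × 20² / 5² = 251.2, so 252 per group, or 252 / 0.8 = 315 with attrition. The stated 140 is not reproduced. That is a separate matter and does not affect this point, which needs only the fact that alpha 0.05 was spent on SBP.

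**Chance error if any one significant result counts as success.** With independent tests the familywise error is 1 − 0.95^k:

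- k = 3 (one visit): 1 − 0.857 = 14.3%
- k = 6 (two visits): 1 − 0.735 = 26.5%

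With correlated tests it was simulated from multivariate normal statistics under no effect, each test rejecting at |z| > 1.96 (2 million draws for three tests, 1 million for six). For six tests, the correlation of two different variables at different visits is the product of the two correlations. The first row is the formula; the others are simulated.

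| SBP–DBP | BP–dose | Between visits | 3 tests, one visit | 6 tests, two visits |
|---|---|---|---|---|
| 0 | 0 | 0 | 14.3% | 26.5% |
| 0.5 | 0.3 | 0.5 | 13.2% | 23.1% |
| 0.7 | 0.3 | 0.7 | 12.6% | 20.3% |
| 0.8 | 0.3 | 0.9 | 12.1% | 16.7% |

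So three tests give about 12% to 14%, and six give about 17% to 26%. The two columns are different scenarios and should not be joined into one range.

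**If all three must be significant,** the familywise error does not exceed 5%. The inflation depends on the decision rule, which the article does not state.

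**Power for SBP under possible remedies.** Completers: 300 × 0.8 = 240 per group. Standard error = 20 × √(2/240) = 1.826, and 5 / 1.826 = 2.739. Power = Φ(2.739 − critical value):

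- at 0.05: Φ(2.739 − 1.960) = 78%
- at 0.05/3 = 0.0167: Φ(2.739 − 2.394) = 63%

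A fixed sequence that starts with SBP keeps the first figure. Under Holm, SBP power lies between the two, depending on whether the other outcomes are rejected first.

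**The case against.** Several objections have force.

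First, a reader might infer that six primary tests are planned. The documents do not say so. Section 2.8 states when the variables are measured, not that each visit carries a primary test. Treatment and follow-up last a year, so month 12 is a natural reading. The six-test figures are a further scenario only.

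Second, the inflation needs an any-one-wins rule, which the article does not state either. This stands as a condition on the figures. It does not remove the point, because no other rule is stated and the text leaves that reading open.

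Third, the 0.05 sentence is compatible with a fixed sequence, in which each test also uses 0.05, and a fuller protocol may contain one. So the correct statement is that the rule is not fixed in this article. Still, section 2.12 presents itself as the analysis plan and fixes a level for every comparison, and the deciding outcome and visit belong with the definition of the primary outcome.

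Fourth, a reader might infer that the chance of a false primary claim would be 5% if multiplicity were handled. It would not. Section 2.4 lets patients choose their group after lectures on anticipated efficacy, and the Discussion accepts that unknown confounders remain. Even a single test at 0.05 has a 5% false-claim rate only if the adjusted groups are comparable.

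Fifth, this is an acknowledged nonrandomized pragmatic study. It treats feasibility as an important purpose and aims to give later randomized trials an ethical basis. How strictly to control multiplicity here is partly judgement. That lowers the urgency, but naming the deciding result in advance costs little in any design.

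**Conclusion.** The point holds in a limited form. The article names three primary variables at two visits and one alpha of 0.05, with no primary visit, order, split or all-required rule, while the sample size is built on SBP alone. The planning alpha is therefore not the error rate of the primary conclusion.

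If any one significant result may be claimed, the nominal familywise chance error is about 12% to 14% for three tests at one visit. Testing both visits would make it about 17% to 26%, but that is not stated. Both ranges rest on assumed correlations. Neither counts the subgroup tests at 0.05 or the optional efficacy look that section 2.10 leaves to the data monitoring committee. Neither includes confounding, which is a separate problem. The defect does not invalidate the study, and it should be corrected before outcome data are seen.

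**What to change.** In sections 2.6.1 and 2.12, state one primary visit and one decision rule for the three outcomes, dated before outcome data are seen. Month 12, the end of the treatment year, would serve as the primary visit, with month 6 supportive. Any of these rules would do:

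- **Fixed sequence starting with SBP at two-sided 0.05.** This keeps the alpha used in section 2.11 and leaves SBP power at about 78% with 240 completers per group. Outcomes later in the order cannot be claimed as confirmed if an earlier one is not significant.
- **Holm across the three.** No order is needed, but SBP power falls from about 78% to as low as about 63%.
- **A declared all-required rule.** Each test stays at 0.05 without inflation, but the power to succeed on all three cannot exceed the 78% for SBP alone.

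The sponsor should choose and justify where drug dose sits. Because dose is adjusted according to blood pressure, a benefit could appear as lower dose with little difference in SBP, and a sequence with dose last could then block that claim.

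The cost is a sentence or two in each section and an update of the registered entry if it does not already say the same. A fixed sequence needs no extra patients on account of multiplicity. None of these rules addresses bias from preference-based allocation.

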### Dissemination plan

2.13

The trial results will be disseminated through webpages and publications in peer-reviewed journals.

### Ethics approval

2.14

This trial has been approved by the ethics committee of the Second Affiliated Hospital of Jiangxi University of Traditional Chinese Medicine (No. 2019-016). The trial will be conducted in compliance with the Declaration of Helsinki and the principles of Good Clinical Practices. Written informed consent will be obtained from all participants.

## Discussion

3

Although acupuncture has long been used to treat hypertension, and there is no lack of evidence supporting its efficacy, it is invasive and must be performed by qualified doctors.^[20]^ Therefore, acupuncture cannot be self-administered by patients or used as a long-term therapy. Heat-sensitive sensitive moxibustion is a noninvasive therapy, and patients can easily learn how to administer it and reach an expected level of efficacy after training. Self-administered moxibustion is also quite inexpensive, costing only approximately 30 Chinese yuan (4 dollars) per month. If our study verifies that heat-sensitive moxibustion does have a significant efficacy for the treatment of hypertension, it may be able to partially replace antihypertensive drugs, reduce medical costs, and serve as a long-term therapy in the community setting. Although a randomized controlled trial is the gold standard for establishing the efficacy of any therapy, it may be ethically problematic without preexisting efficacy and safety evidence. Therefore, this nonrandomized pragmatic study also aims to provide an ethical basis for further randomized controlled trials.

In 2017, the government of Xiashan District in Weifang city in Shandong Province tried for the first time to popularize heat-sensitive moxibustion as a daily health care method for all residents of the town. The measures taken to popularize the knowledge of heat-sensitive moxibustion included building a community center dedicated to providing free sessions of heat-sensitive moxibustion, organizing expert lectures, training patients on-site, and providing free moxibustion materials. After 2 years of efforts, the popularization work achieved satisfactory results – heat-sensitive moxibustion was practiced by 67% of the total population of 62,000 people. In addition, the per capita medical expenditure decreased by 49.8% and the number of annual outpatient consultations decreased by more than 16.7% compared with the values 2 years before.^[21]^ Unfortunately, no rigorous evidence was obtained regarding the effects of heat-sensitive moxibustion on hypertension with the exception of scattered case reports published during the popularization campaign. Learning from the successful experience in Shandong Province, the government of Jiangxi Province started to promote a public health project called “Everyone Uses Heat-sensitive Moxibustion, Everyone Enjoys Health” in several cities in 2019. Currently, the project is progressing smoothly. It could provide a favorable climate for the recruitment of participants and the successful completion of this study.

This study has potential limitations. The reduction of internal validity caused by the nonrandomized design is the main limitation. Although we have expanded the expected sample size as much as possible and will adjust for multiple confounders in the statistical analysis, the bias caused by unknown confounders cannot be completely avoided. However, the extrapolation of the results of this study, as a major advantage of a pragmatic study, will be enhanced. Another limitation is that it may be difficult for patients to remain compliant with the heat-sensitive moxibustion protocol for 1 year, and poor compliance will introduce bias. However, an important purpose of this study is to evaluate the feasibility of heat-sensitive moxibustion self-administration as a long-term intervention in patients in the community with hypertension. If compliance is poor, it will show that this is not a feasible strategy.

In summary, with the increasing incidence of hypertension, it is imperative to emphasize community-based management. Heat-sensitive moxibustion self-administration has potential advantages in terms of efficacy and compliance. The findings of this study will provide the first pragmatic evidence of the effect of heat-sensitive moxibustion self-administration by patients in the community on primary hypertension and may impact the government's public health decisions.

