### Site and participant recruitment

2.2

We will recruit patients with primary hypertension from 4 communities: the Nangang community, the Honggutan community, the Shengmi community in Nanchang city, and the Gaofu town community in Fu Zhou city. Recruitment will occur through community doctors’ oral communication with individuals, posters, and mobile advertising. Patients who express a preliminary willingness to participate in the study will be screened for eligibility and informed about the entire study process, benefits, and potential harms. Eligible patients will formally enter the study cohort after signing the informed consent form. The overall study design is shown in Figure 1.

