### Eligibility criteria

2.3

A patient will be eligible to participate in this study if he or she has been diagnosed with primary hypertension according to American College of Cardiology/American Heart Association criteria (ie, systolic blood pressure [SBP] ≥ 130 mm Hg or diastolic blood pressure [DBP] ≥ 90 mm Hg),^[17]^ is between 18 and 70 years old and is willing to sign the informed consent form. However, the following patients will be excluded:

(1)patients with hypertension secondary to pregnancy; brain, macrovascular, kidney or endocrine disease; or drug-induced factors;(2)patients who are allergic to moxa, moxa smoke, or the moxibustion device;(3)patients who are pregnant or lactating;(4)patients who have experienced serious cardiovascular and cerebrovascular events (eg, myocardial infarction and stroke);(5)patients with other severe diseases, such as liver and kidney dysfunction indicated by a level more than 2 times the upper limit of normal for total bilirubin, alanine aminotransferase, aspartate aminotransferase or serum creatinine; malignant tumors; and major mental disorders.

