### Interventions and co-interventions

2.5

Patients in the heat-sensitive moxibustion group will self-administer heat-sensitive moxibustion for one year while maintaining their original antihypertensive drugs. With the doctors’ help, the patients will first identify the heat-sensitive acupuncture points near CV8 (Shenque, the center of the navel), CV4 (Guanyuan, approximately 10 cm below the navel), and bilateral ST36 (Zusanli, approximately 7 cm below the lateral of the knee) and then perform moxibustion on the heat-sensitive acupoints. Self-sticking mini-moxa rolls will be used as the combustible material, which can be placed and burned in a moxibustion box (Fig. 2). A matching velvet bag can be used to wrap the moxibustion box to avoid burns. The suggested dose of moxibustion will be one moxa roll (approximately 30 minutes) per session, with 1 session per day and 7 sessions per week. Driven by a pragmatic design, we will allow the patients to adjust the dose of moxibustion to make it convenient, but they need to truthfully report the adjusted dose. Patients in the control group will only maintain their original antihypertensive drugs and will not perform heat-sensitive moxibustion. There will be no restriction on the type and dose of antihypertensive drugs, but other acupoint stimulation therapies, such as acupuncture, will be prohibited.

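### Current and past heat-sensitive moxibustion use is missing from the exclusions, baseline data and covariates, although patients choose their group while a campaign promotes the therapy

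*Protocol article*

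**What the plan says.** - **Campaign.** The Discussion says that the Jiangxi government began promoting heat-sensitive moxibustion in several unnamed cities in 2019, and comments: "It could provide a favorable climate for the recruitment of participants". The trial was registered in May 2020 (Study design). For an earlier campaign in a district of another province, the Discussion reports that "heat-sensitive moxibustion was practiced by 67% of the total population of 62,000 people" after two years.
- **Recruitment.** "Recruitment will occur through community doctors’ oral communication with individuals, posters, and mobile advertising" (Site and participant recruitment). The campaign is not listed as a channel.
- **Allocation.** Patients attend lectures on the therapy and its anticipated efficacy, then enter the group they prefer (Training and assignment).
- **Exclusions.** Five are itemised. The only one that concerns moxibustion is "patients who are allergic to moxa, moxa smoke, or the moxibustion device" (Eligibility criteria).
- **Baseline data.** The month 0 list goes down to "smoking, drinking, and type and dosage of antihypertensive drugs currently used" (Study visits). Moxibustion history is not on it.
- **Analysis.** The ANCOVA and logistic models adjust for eight named factors, including baseline SBP but not prior moxibustion use. The intention-to-treat rule foresees "patients in the control group who performed heat-sensitive moxibustion" and keeps them as controls. Per-protocol analyses are a sensitivity check for the primary outcomes and the only analysis for the secondary ones (Statistical analysis plan).
- **Controls.** They are not to use heat-sensitive moxibustion, and "other acupoint stimulation therapies, such as acupuncture, will be prohibited" (Interventions and co-interventions).

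**The concern.** The plan intends to compare starting moxibustion with not starting it. Nothing in it separates patients who start from patients who were already using the therapy. With allocation by preference, existing users would be expected to gather in the moxibustion group, for two reasons: they like the therapy, and controls must abstain.

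Three things are at stake.

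- **Blood pressure.** The primary outcome is change in pressure. If an existing user's baseline already contains the effect, little further change is left to observe, and the group difference shrinks. The same reasoning applies to percentage change in drug dose if doses had already been reduced before entry.
- **Compliance and safety.** Existing users have shown that they tolerate the therapy and keep it up. Their presence may make compliance and adverse-event rates look better than in people who start at enrolment. The Discussion calls feasibility of long-term self-administration an important purpose of the study.
- **No later repair.** The Discussion's limitations name unknown confounders. Prior use is a known and measurable one, but if it is not recorded at month 0 no analysis can adjust for it afterwards.

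**Working it through.** The document states no figure on prior use, so there is none to reproduce. The check has two parts.

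**1. The lists side by side**

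| Place | Itemised content on moxibustion |
|---|---|
| Eligibility criteria | Allergy only; no current or past use, no washout |
| Study visits, month 0 | None |
| Statistical analysis plan, covariates | None |

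The omission is the same in all three lists.

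**2. Illustrative size for SBP**

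Inputs:
- True effect 5 mm Hg (Sample size calculation).
- *s*, the share of existing users in the moxibustion group: not given; assumed 10%, 20% and 30%.
- *b*, the slope of follow-up SBP on baseline SBP: not given; assumed 0.5.
- Assumptions: existing users enter with SBP already 5 mm Hg lower and show no further change; new users fall by 5 mm Hg; controls do not change and none uses moxibustion; the groups are otherwise alike.

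Derivation:
- At follow-up every moxibustion patient is 5 mm Hg below the untreated level, so the groups differ by 5.
- At baseline the moxibustion group is already lower by 5 × *s*.
- Unadjusted change: 5 − 5*s* = 5 × (1 − *s*).
- ANCOVA on baseline SBP: 5 − *b* × 5*s* = 5 × (1 − *b* × *s*).

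| *s* (assumed) | Baseline gap, 5 × *s* | Unadjusted change | ANCOVA, *b* = 0.5 |
|---|---|---|---|
| 10% | 0.5 | 5 × 0.90 = 4.5 | 5 × 0.95 = 4.75 |
| 20% | 1.0 | 5 × 0.80 = 4.0 | 5 × 0.90 = 4.5 |
| 30% | 1.5 | 5 × 0.70 = 3.5 | 5 × 0.85 = 4.25 |

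All entries are in mm Hg except *s*. At *b* = 1 the ANCOVA result equals the unadjusted one; at *b* = 0 there is no dilution. At 20% existing users the range over *b* from 1 to 0 is therefore 4.0 to 5.0 mm Hg. The unadjusted column is the worst case, and the planned ANCOVA lessens the bias without removing it.

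**Control use** acts differently. If a share *c* of controls starts moxibustion after baseline and gets the full effect, the difference is 5 × (1 − *c*), for example 4.5 mm Hg at an assumed 10%. Baseline adjustment does not reduce this.

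**The case against.** The strongest case on the other side has four parts.

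- **The campaign link is loose.** A reader might infer that recruitment relies on the campaign. The document does not support this: it says only that the campaign could help, gives other recruitment channels, and does not say that Nanchang or Fu Zhou is among the campaign cities. What stands is that the authors expect the campaign to favour recruitment, which makes sense only if it reaches people who might enrol.
- **Control use may well be recorded.** A reader might infer that it goes untracked and that the per-protocol set cannot find control users. That reads silence as a defect. The analysis section foresees control users, and a per-protocol set presupposes that they are identified. Patients in both groups attend visits, and the visit-schedule figure and case report forms are not shown. What stands is narrower: the article describes no method. Compliance is defined by moxibustion frequency, and the soot check uses boxes supplied to the moxibustion group.
- **The size is assumed.** A reader might treat the 67% uptake as a local estimate; it comes from another province. A reader might also turn the worst case into lost power: with 240 analysed per group (300 less 20%) and SD 20, power falls from about 78% at 5 mm Hg to 69%, 59% and 48% at 4.5, 4.0 and 3.5. Those figures belong to an unadjusted change score, not to the planned ANCOVA, whose residual variance is not given.
- **Nonrandomised confounding is already conceded.** True, but in terms of unknown confounders and poor compliance. That does not cover a factor that one question would capture.

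Condensation does not explain the main gap, because eligibility, baseline data and covariates are each set out item by item.

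**Conclusion.** The concern holds as a gap in what the protocol fixes: prior and current use of the study therapy is absent from the exclusions, the month 0 data and the adjustment set, under preference-based allocation and alongside a campaign for the same therapy.

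Its effect on SBP is a risk of unknown size. Under the assumptions above, 10% to 30% existing users would reduce an expected 5 mm Hg difference by 0.25 to 0.75 mm Hg under ANCOVA (slope 0.5), and by 0.5 to 1.5 mm Hg at worst. Whether any existing users will enrol is not known.

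It would be tempting to say that the direction of bias is settled. It is not. The already-treated baseline pulls toward no difference, while tolerance of the therapy and belief in it may push results, compliance and safety the favourable way. That uncertainty is itself a reason to record use.

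**What to change.** 1. **Study visits, month 0:** add current and past moxibustion use for all patients in both groups.
2. **Statistical analysis plan:** repeat the primary analysis in patients not using moxibustion at entry, or add prior use to the covariates. If nearly all current users choose moxibustion, the covariate has few controls to compare them with, so the restricted analysis is easier to interpret.
3. **Monthly visits:** ask about any moxibustion use in both groups, and use the answers to define the per-protocol set. This matters most for the secondary outcomes, which have no other analysis population.

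The cost is one baseline question, one question at visits that already take place, and one sensitivity analysis on fewer patients. With 240 moxibustion patients analysed (300 × 0.8), assumed shares of 10% to 30% existing users would leave 216 to 168 of them (240 × 0.9 to 240 × 0.7) in the restricted analysis. The main intention-to-treat analysis loses no one.
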